### Study duration

Recruitment will continue for 18 months. Follow-up for 6 months with 6 months for analysis.

### Economic evaluation

The economic feasibility will focus on data collection to inform the economic evaluation to be done alongside the definitive trial. As well as the EQ-5D-5L and ICECAP-A we will record length of stay in both study arms, along with time spent in theatre and implants used (surgical arm only). Use of specific primary, community and social care services will be assessed by patient reported resource use questionnaires at 6 weeks, 3, 6, 9 and 12 months.

### Qualitative study

To inform the conduct of the definitive trial, we will invite up to 20 consented participants (10 from each treatment arm and across all sites) to take part in a semi-structured telephone interview by the qualitative researcher after they have completed the 6-month follow-up questionnaire. The interviews will explore their experience of the trial, their treatment and recovery, and acceptability of the outcome measures. A purposive sample will be selected to reflect maximum variation in socio-demographics, age and ethnicity. Topic guides for the interviews will be developed from the literature, team discussions and input from the PAG. Ten participating healthcare professionals (surgeons, research nurses and clinical nurse specialists) will be invited to take part in a telephone interview evaluating their experiences of treatment and views of trial processes.

### Safety reporting

Only serious adverse events will be reported for this study comparing two treatments in common clinical practice. A serious adverse event is any untoward medical occurrence that:

Results in death.Is life-threatening.Requires inpatient hospitalisation or prolongation of existing hospitalisation.Results in persistent or significant disability/incapacity.Consists of a congenital anomaly or birth defect.

Serious adverse events which are expected with these injuries are:

Wound complications/infections.Neurovascular injury.Thromboembolic events.Chest infection.Metal work/implant failure/loosening and non/mal-union.

Secondary operations to prevent infection, mal-union, non-union or for symptoms related to the metalwork may also be expected.

Any unexpected serious adverse events will be recorded and reported to the Sponsor and Ethics Committee.

### Sample size

This feasibility study is designed to produce estimates of the parameters required to plan a definitive trial, together with enough data on outcome measures to show whether or not the ceiling effect on the Iowa instrument is likely to be a problem in the definitive trial. If 120 patients are screened as eligible and 40% agree to take part, then this will allow us to estimate the recruitment rate of 40% with a 95% CI of 31%–49% which is within 10% in either direction. Forty complete sets of data should be enough to show when a ceiling effect starts to occur although this will rely on a visual inspection of the data at each time point. If 60 sets of data are collected this will allow greater precision.

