### Aim and objectives

The overarching aim is to perform a definitive trial to establish whether surgical or non-surgical management of unstable LC1 fractures is most appropriate. The aim of this feasibility study is to allow us to plan a full definitive trial by measuring recruitment, retention and follow-up rates and explore participant and staff views of the trial processes. Study objectives are shown in box 1.

Box 1Detailed study objectivesTo produce a Consolidated Standards of Reporting Trials diagram, reporting screening, recruitment, randomisation compliance and include allocation proportions by centre.To confirm the recruitment rates and percentage of eligible patients who agree to take part.To collect outcome data at fixed time points post injury to collate the completeness and spread of the data at different time points post injury.To identify the outcome measure to be used as the primary outcome on the basis of completeness of data, sensitivity to change over time, the presence of floor or ceiling effects and patient acceptability.To develop and refine methods for the collection of resource use data relating to both management pathways.To explore patient and staff views of randomisation, treatment and trial processes using qualitative interviews.

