### Measures at baseline and follow-up

*Iowa Pelvic Score*: A measure specific to outcomes following pelvic injury.^12^ Shows good construct validity when compared with the physical component of the SF-36. This is also the preferred pelvic specific outcome measure by patients^13^ and the study patient advisory group.

*Oxford Hip Score*
14: A functional score for patients following hip injury and/or surgery. While not pelvic specific, the activities and symptoms included were felt to be relevant by our patient group.

*EQ-5D-5L*
15: A standardised instrument of health status.

*ICECAP-A*
16: A measure of capability for the general adult population for use in economic evaluation. It focuses on well-being in the broader sense, not just health status.

*Brief Pain Inventory*
17: Originally developed to measure pain in patients suffering from cancer. It has since been used in a variety of conditions. It allows patients to rate the severity of their pain as well as its influence on their psychological health and activity

All participants will complete these questionnaires at baseline, 2 and 6 weeks, 3 and 6 months following randomisation. Participants recruited in the first 12 months of the study will also complete questionnaires at 9 and 12 months following randomisation. Baseline data will be collected at recruitment. Participants will be able to complete their follow-up questionnaires in person, when attending an outpatient appointment, online or by post. Standard care for participants with these injuries would be for clinical review in an outpatient clinic at 6 weeks, 3 months and 12 months (see table 1).

**Table 1 T1:** Visit schedule

	Baseline	2 weeks* (+1 week)	6 weeks* (±1 week)	3 months* (±2 weeks)	6 months* (±3 weeks)	9 months* (±3 weeks)	12 months* (±4 weeks)
	Inpatient	Phone/online	Clinic	Clinic	Post/online	Post/online	Clinic
Demographics	✓						
Injury characteristics	✓						
Clinical review	✓	✓†	✓	✓			✓
Surgical details		✓‡					
Rehabilitation		✓	✓	✓	✓	✓	✓
Adverse events	✓	✓	✓	✓	✓	✓	✓
Iowa Pelvic Score	✓§	✓	✓	✓	✓	✓	✓
OHS	✓§	✓	✓	✓	✓	✓	✓
EQ-5D-5L	✓§	✓	✓	✓	✓	✓	✓
ICECAP-A	✓	✓	✓	✓	✓	✓	✓
BPI	✓§	✓	✓	✓	✓	✓	✓
TUAG			✓	✓			✓
Resource use			✓	✓	✓	✓	✓

*From date of randomisation.

†Non-operative group only.

‡Surgical group only.

§Preinjury and postinjury.

BPI, Brief Pain Inventory; EQ-5D-5L, Euroquol - 5 Dimension - 5 level; ICECAP-A, ICEpop Capability measure for Adults; OHS, Oxford Hip Score; TUAG, Timed Up and Go.

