### Data analyses

#### Quantitative data analysis

As this is a feasibility trial no formal statistical testing will be carried out. Instead the analysis will focus on reporting data that will be used for planning and for assessing the feasibility of the definitive trial.

Feasibility parameters with 95% CIs will be provided using the exact binomial method. The spread of the data and ceiling effects will be documented for all outcome variables using histograms for single time points and box plots to compare over time. Calculation of the area under the curve over time is the likely primary method of analysis for the definitive trial, and the feasibility analysis will investigate whether this would produce a sufficiently complete data set or whether it would be better to focus on a particular time point. The 95% CI for the effect sizes for all potential outcome measures will be calculated to ensure that a future trial can be planned appropriately.

The future economic evaluation is likely to present results in cost/Quality Adjusted Life Year (QALY) terms reporting within trial and lifetime horizons. The economic feasibility work will focus on establishing the appropriate methods for collecting the outcomes, both costs and utilities, which will be of interest in the future economic evaluation, with analysis therefore limited to assessment of completeness and descriptive statistics.

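### The Iowa ceiling effect is to be judged by eye from one-measure plots, which neither estimate the share of patients at the limit nor show whether those patients still have problems

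*Protocol article*

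**What the plan says.** The Sample size section gives the study two tasks: to estimate the planning parameters, and to collect enough outcome data "to show whether or not the ceiling effect on the Iowa instrument is likely to be a problem in the definitive trial". On the second it states: "Forty complete sets of data should be enough to show when a ceiling effect starts to occur although this will rely on a visual inspection", made separately at each time point. It adds: "If 60 sets of data are collected this will allow greater precision". Neither number of data sets comes with an expected share of patients at the limit or a precision for that share.

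The Quantitative data analysis section names the displays: "ceiling effects will be documented for all outcome variables using histograms for single time points and box plots to compare over time". It also rules out formal testing and plans exact binomial 95% CIs for feasibility parameters.

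Box 1 (Aim and objectives) bases the choice of primary outcome on completeness of data, "sensitivity to change over time, the presence of floor or ceiling effects and patient acceptability".

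Table 1 (Measures at baseline and follow-up) schedules all five questionnaires at every visit. At baseline it marks Iowa, OHS, EQ-5D-5L and BPI as "Preinjury and postinjury".

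**The concern.** Whether a ceiling would matter in the definitive trial turns on two things: how many patients sit at the best score, and whether those patients still differ in ways the score misses. The named displays handle the first only roughly and do not reach the second. A fully recovered patient and a patient with limitations that the Iowa items do not register fall in the same histogram bar.

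What is at stake is the choice of primary outcome. Iowa is the pelvic-specific score, and the article reports that patients and the study's advisory group prefer it. With no estimate and no link to other measures, two readers of the same plots could reasonably differ on whether the score has a ceiling problem. The definitive trial would then inherit a choice that cannot be checked against a reported figure.

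**Working it through.** **Inputs.** 120 eligible patients and 40% consent; 40 or 60 data sets (Sample size). Exact binomial intervals (Quantitative data analysis). 18 months of recruitment (Study duration). Questionnaires at 9 and 12 months only for those recruited in the first 12 months (Measures at baseline and follow-up). The shares at the best score used below are assumptions.

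**1. The plan's own figure.** 40% of 120 is 48. The normal approximation gives 0.40 ± 1.96 × √(0.40 × 0.60 / 120) = 0.40 ± 0.088, or 31.2% to 48.8%. The exact interval is 31.2% to 49.3%. Both round to the stated 31% to 49%, so that figure is right. It concerns recruitment; the 40 and 60 data sets have no calculation behind them.

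**2. Precision of the share at the limit.** For x of n patients, the exact limits are the 0.025 quantile of Beta(x, n − x + 1) and the 0.975 quantile of Beta(x + 1, n − x).

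| Assumed share | n = 40 | n = 60 |
|---|---|---|
| 10% | 4/40: 2.8% to 23.7% | 6/60: 3.8% to 20.5% |
| 15% | 6/40: 5.7% to 29.8% | 9/60: 7.1% to 26.6% |
| 20% | 8/40: 9.1% to 35.6% | 12/60: 10.8% to 32.3% |
| 30% | 12/40: 16.6% to 46.5% | 18/60: 18.8% to 43.2% |

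These intervals show how rough the estimate is. They do not bear on recovery versus lost discrimination, which is a matter of what information is used and is not cured by moving from 40 to 60.

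**3. What the plots can carry.** Take a score whose best value is its highest. A box plot extends to the maximum once a single patient is there (1/40 = 2.5%), but the upper edge of the box reaches it only when about a quarter are there (10/40). So 1/40 and 8/40 (20%) at the maximum can look much alike. A histogram shows the share better, but the reading depends on bin width and carries no interval.

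Nor do separate plots for each instrument link patients. Suppose 6 of 40 are at the best Iowa score and 6 of 40 at the best OHS. The number at both can be anything from max(0, 6 + 6 − 40) = 0 to 6, and the two histograms are the same throughout.

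**4. Limits of a cross-check.** With 6 patients at the best Iowa score, finding 3 of them with remaining problems has an exact 95% CI of 12% to 88%. Such a table can inform judgement but cannot carry a decision rule.

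**5. Numbers actually available.** Forty complete sets from 48 recruits need 40/48 = 83% completeness, and 60 recruits need 60/120 = 50% consent. If accrual is even (an assumption), about 48 × 12/18 = 32 patients are due questionnaires at 9 and 12 months before any loss; 5/32 has an exact CI of 5.3% to 32.8%.

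**The case against.** The strongest reply is that this is a feasibility study without testing, for which descriptive graphics are ordinary, and that a percentage at the limit or a cross-instrument table may stand in an analysis plan that is not shown. That is fair as far as missing detail goes: the absence of a threshold is not an error. But the article does not leave the method open. It says the ceiling judgement rests on visual inspection and names the plots.

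A second reply is that the displays cover all outcome variables, so Iowa piling up while OHS or BPI stays spread would be visible. This stands in part. Comparison at group level is possible; what is not described is any linkage within patients. Interviews after the 6-month questionnaire cover recovery and acceptability of the measures, but in at most 20 participants.

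Three stronger readings are tempting and are not supported:

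- A reader might infer that the study cannot tell recovery from a ceiling. It collects data that bear on this; only the joint use is undescribed.
- A reader might infer that pre-injury scores lie near the maximum, so that recovery alone would produce a pile-up. The article gives no such scores, and its Background cites a study in which patients had not regained pre-injury function at 24 months.
- A reader might infer that looking for ceilings inspects the wrong end of some scales. The Abstract, Box 1 and Outcomes sections all name floor as well as ceiling effects, and a histogram shows both ends.

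**Conclusion.** The point holds as a choice of method that can be improved cheaply. A stated design purpose, which also feeds one of four criteria for the primary outcome, rests on inspection of plots that show each instrument's distribution separately. They give no estimate with uncertainty of the share at the limit, and they do not show whether patients at the best Iowa score still have problems the score misses.

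On size: at an assumed 15% at the best score, 40 sets leave a range of 6% to 30% and 60 sets 7% to 27%, so calling forty sets sufficient suggests more certainty than they give. The error in the eventual choice of outcome cannot be quantified, because the article gives no score distributions and no rule by which a ceiling would exclude an instrument. The conclusion does not depend on the assumed shares, which only illustrate precision.

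**What to change.** In the Sample size and Quantitative data analysis sections, replace visual inspection as the basis for judgement with the following, and keep the histograms and box plots as illustration.

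1. For each questionnaire score and visit, report the proportion at the best and at the worst possible score, each with an exact binomial 95% CI. Exclude Timed Up and Go, which is a time and has no best possible score.
2. Among patients at the best Iowa score at a visit, tabulate descriptively their pre-injury Iowa score and their OHS, BPI and EQ-5D-5L at that visit. Read the generic measures alongside Injury Severity Score, since other injuries may explain remaining problems.
3. If a reference threshold is wanted, for example 15%, it is the sponsor's choice, best fixed in advance. It should guide interpretation and not act as a rigid rule: at 6/40 the interval lies on both sides of 15%.

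No new data and no hypothesis test are needed. The cost is a few extra tables with wide intervals, which will show openly that 40 sets give only a rough answer.

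### The 40 and 60 complete data sets in the sample size section are not reconciled with 48 expected recruits, of whom only about 32 are due questionnaires at 9 and 12 months

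*Protocol article*

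**What the plan says.** The Sample size section of the protocol article gives the study two purposes: to estimate parameters for planning a definitive trial, and to show whether a ceiling effect on the Iowa instrument is likely to be a problem.

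- For the first purpose it assumes: "If 120 patients are screened as eligible and 40% agree to take part". This is said to "estimate the recruitment rate of 40% with a 95% CI of 31%–49" per cent.
- For the second it says: "Forty complete sets of data should be enough to show when a ceiling effect starts to occur". It adds that "this will rely on a visual inspection of the data at each time point", and then: "If 60 sets of data are collected this will allow greater precision".

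The follow-up schedule is set elsewhere. Under Measures at baseline and follow-up, every participant is due at baseline, 2 and 6 weeks, and 3 and 6 months. After that: "Participants recruited in the first 12 months of the study will also complete questionnaires at 9 and 12 months following randomisation". Under Study duration: "Recruitment will continue for 18 months", followed by 6 months of follow-up.

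The Sample size section does not mention the shortened follow-up of later recruits. It makes no allowance for loss, does not define a complete set, and does not link the 40 or the 60 to the number of recruits that its own assumptions imply.

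**The concern.** The section offers 40 sets as enough to show when the ceiling effect begins. Answering that requires looking along the whole follow-up, including 9 and 12 months. Those are the time points at which the schedule leaves out everyone recruited after month 12, so the number available there can fall well below 40 with perfect return. The 60-set scenario has a simpler problem: it exceeds the number of recruits the same paragraph implies.

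Ceiling and floor effects and completeness of data are among the stated grounds (Box 1) for choosing the definitive trial's primary outcome. If an outcome measure reaches its ceiling only late in recovery, that will be judged on the smallest group in the study. The criterion is visual, so the plan puts no figure on the uncertainty of that judgement. A reader of the Sample size section would not learn this.

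**Working it through.** **Inputs from the article:** 120 eligible; 40% consent; 40 and 60 sets; 18 months of recruitment; late questionnaires for those recruited in the first 12 months; 6 months of follow-up after recruitment closes.

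**Assumptions, not in the article:** the shape of accrual and the loss to follow-up. I also read the first 12 months as months of recruitment. That fits the timetable, because a month-12 recruit reaches 12 months of follow-up at month 24, and 18 + 6 = 24.

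**1. The plan's own figure.** Recruits = 120 × 0.40 = 48. The Wald interval is 0.40 ± 1.96 × √(0.40 × 0.60 / 120) = 31.2% to 48.8%. The exact binomial interval for 48/120 is 31.2% to 49.3%. Both round to the stated 31%–49%, so this figure is correct.

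**2. Time points up to 6 months.** All 48 are due. Forty sets need 40/48 = 83% completion. With 10% loss, 48 × 0.9 = 43.2 sets; with 20% loss, 48 × 0.8 = 38.4.

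**3. Time points at 9 and 12 months.** Number due = 48 × (share recruited in the first 12 months).

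| Accrual (assumed) | Due at 9 and 12 months, before loss |
|---|---|
| Even: 48 × 12/18 | 32 |
| Linear start-up over 3 months | 30.5 |
| Linear start-up over 6 months | 28.8 |
| Linear start-up over 12 months | 24.0 |
| Front-loaded, 83% in the first 12 months | 40 |

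With even accrual and 10%, 20% or 30% loss, 32 becomes 28.8, 25.6 or 22.4. To have 40 sets at these time points under even accrual, the study would need 40 ÷ (12/18) = 60 recruits with no loss, or 60 ÷ 0.8 = 75 with 20% loss.

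As a sensitivity check, take the ends of the plan's interval as alternative consent rates. Recruits are then 0.31 × 120 = 37.2 or 0.49 × 120 = 58.8. Two-thirds of these is 24.8 or 39.2, so even the upper end falls just short of 40 before loss.

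**4. Sixty sets.** Sixty exceeds 48 at every time point. It needs 60 ÷ 0.40 = 150 eligible patients, or 60 ÷ 120 = 50% consent, and in either case no loss even up to 6 months.

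**5. What the shortfall costs in precision.** For an assumed 20% of participants at the maximum score, the half-width of a 95% interval is 1.96 × √(0.20 × 0.80 / n):

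| n | Half-width, percentage points |
|---|---|
| 32 | 13.9 |
| 40 | 12.4 |
| 48 | 11.3 |
| 60 | 10.1 |

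**The case against.** The strongest reply is that nothing here was promised. The 48 rests on a conditional, the 60 is also conditional, and 40 is a hedged judgement for descriptive plots in a study without formal testing. The phrase about each time point qualifies the visual inspection and does not guarantee 40 sets at every visit. All 48 recruits are followed to 6 months, so a ceiling that begins by then can be seen as planned. The Iowa score is also collected for the pre-injury state at baseline in everyone, which shows in the full sample whether normal function sits at the maximum. And 32 depends on an accrual curve that the article does not give.

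Most of this stands and limits the point. A reader might infer that 32 is an upper bound, or that 40 late sets are impossible. Neither follows: front-loaded accrual would give more than 32, and a slow start across nine centres would give fewer. Nor do the documents support saying that the ceiling-effect aim fails, since 40 sets are attainable up to 6 months at 83% completion.

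The reply does not close the gap. The section itself names 40 as enough to show when the effect starts, and the article's own schedule is not expected to supply 40 at the last two time points. Pre-injury scores bear on whether a ceiling exists, but not on when recovering patients reach it. A scenario can be conditional and still need to be compatible with the assumptions in the same paragraph, and 60 from 48 is not.

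**Conclusion.** The point holds as a failure to reconcile the stated size with the schedule, and it is of moderate weight. On the plan's figures 48 participants are due up to 6 months. About 32 are due at 9 and 12 months under even accrual before loss, and 24 to 31 under the start-up patterns tried. The 40-set claim is therefore reasonable to 6 months if completion reaches 83%, and is not expected to be met afterwards. If a complete set means every time point to 12 months, the expected total is itself about 32. The 60-set scenario does not fit 120 × 40% at any time point.

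The consequence is limited: about 1.5 percentage points of half-width between 32 and 40 sets at an assumed 20% at ceiling (13.9 − 12.4). No stated result becomes invalid, and the recruitment-rate interval is correct.

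A reader might go further and infer that the area under the curve will look incomplete for administrative reasons. The article asks only "whether this would produce a sufficiently complete data set". It fixes neither the time span of the curve nor the denominator for completeness, and those details can properly sit in the statistical analysis plan. The documents do not support a finding there.

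**What to change.** 1. In the Sample size section, give the expected number of sets by time point, with the accrual and retention assumptions behind them: about 48 due to 6 months, and about 32 due at 9 and 12 months under even accrual, before loss.
2. Confine the claim that 40 sets are enough to time points up to 6 months, and say that it needs 83% completion.
3. Delete the 60, or state what it requires: 150 eligible patients at 40% consent, or 50% consent among 120, with no loss.
4. Alongside the planned histograms and box plots, report the proportion at the maximum and at the minimum score at each time point with its exact 95% CI. Restrict this to participants due at that time point, and show the numbers due and returned. The article already uses the exact binomial method for its feasibility parameters, so no new method is needed.

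The cost is a change of wording and a small addition to the descriptive analysis. The stated precision at 9 and 12 months becomes less favourable. No extra patients and no change to data collection are needed.
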